### Overall Design:

ACCORD-2 is a seamless, Phase 2, adaptive, randomisation platform study, designed to rapidly test candidate agents in the treatment of COVID-19 disease. The study will include hospitalised adult patients ( $\geq 18$  years) who have infection with SARS-CoV-2, the virus that causes COVID-19, as confirmed by laboratory tests and/or point of care tests. For inclusion, patients will need to have clinical status of Grade 3 (hospitalised – mild disease, no oxygen therapy) to Grade 5 (hospitalised – severe disease, noninvasive ventilation or high-flow oxygen), as defined by a 9-point ordinal scale.

This study will aim to identify efficacious candidate agents for treatment of COVID-19 disease. These candidate agents may include, but will not be limited to, anti-virals, human plasma-derived agents, or immunomodulatory agents. Experimental (first-in-human) agents will not be considered as candidate agents for ACCORD-2, but will instead be considered for inclusion in the separate, but linked, ACCORD-1 Phase 1/2 platform study, which will first determine the dose and assess early activity and safety signals for later consideration for inclusion into ACCORD-2. The ACCORD-2 candidate agents evaluated will include those intended as a treatment for SARS-CoV-2 infection; the study design and/or inclusion and exclusion criteria may subsequently be revised (using a protocol amendment) or a separate protocol may be initiated to include agents intended to prevent COVID-19 disease.

This Master Protocol outlines the overall structure of the study, including the population, inclusion and exclusion criteria, randomisation scheme, primary, secondary, and exploratory outcomes, study design, statistical methodology, and planned analyses that are common for all candidate agents to be tested. The Master Protocol is structured such that multiple candidate agents from different pharmaceutical companies can be evaluated simultaneously. The plan is to add candidate agents as they are identified, and to remove therapies once they have completed their evaluation, with the control group for a candidate agent including only patients randomised during the period in which the candidate agent group was randomised, with patients being randomised equally (ie, 1:1:1...) to the sub-protocols with inclusion/exclusion criteria that they meet.

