This Master Protocol outlines the overall structure of the study, including the population, inclusion and exclusion criteria, randomisation scheme, primary, secondary, and exploratory outcomes, study design, statistical methodology, and planned analyses that are common for all candidate agents to be tested. The Master Protocol is structured such that multiple candidate agents from different pharmaceutical companies can be evaluated simultaneously. The plan is to add candidate agents as they are identified, and to remove therapies once they have completed their evaluation, with the control group for a candidate agent including only patients randomised during the period in which the candidate agent group was randomised, with patients being randomised equally (ie, 1:1:1...) to the sub protocols with inclusion/exclusion criteria that they meet.

Sub-protocols will outline the scientific rationale, eligibility, treatment schema, and other specifics for each candidate agent. The sub-protocols may define adverse events of special interest (AESIs), and can include pharmacokinetic and/or pharmacodynamic assessments that are appropriate for the specific candidate agent (pharmacodynamic assessments may require

equivalent blood samples from controls). Additional patients will be recruited into the study each time a new sub-protocol (candidate agent) is added.

The study consists of 2 stages:

- **Stage 1** of the study (evaluation/pilot) will evaluate the candidate agents as an add-on to the standard of care (SoC) to assess preliminary safety and efficacy. A patient will be considered to be a responder if they show an improvement of at least 2 points (from randomisation) on a 9-point category ordinal scale, are discharged from hospital, or are considered fit for discharge (a score of 0, 1, or 2 on the ordinal scale), whichever comes first, by Day 29. The time to response will be analysed on Day 29 and used to evaluate if an agent should proceed to Stage 2 of the study. Stage 1 data will additionally be used to determine optimal study endpoints, and the number of patients to enrol into Stage 2 of the study.

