## **4.2 Scientific Rationale for Study Design**

There are currently no approved therapeutic agents available to treat coronaviruses such SARS-CoV-2, the causative agent of as COVID-19 disease, and there is an urgent public health need for rapid development of such interventions. This adaptive platform study is designed to rapidly assess multiple candidate agents as treatments for COVID-19. Candidate drugs that are initially assessed as being efficacious will be moved from an evaluation (pilot) stage to a confirmatory stage, with candidate agents being added to and removed from the study on an ongoing basis, depending on the results of their evaluation. Patients to be included in the study will be hospitalised and may require either supplemental oxygen, noninvasive ventilation or high-flow oxygen devices.

This study utilises an adaptive design that maximises efficiency in identifying a safe and efficacious therapeutic agent for COVID-19. Some candidate agents may be in limited supply and this study design enables continuation of the study even if an agent becomes unavailable. In addition, the adaptive design allows for the evaluation of new candidate agents as they are identified.

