## 5.0 STUDY POPULATION

Prospective approval of protocol deviations to recruitment and enrolment criteria, also known as protocol waivers or exemptions, is not permitted.

The inclusion and exclusion criteria listed below may be supplemented by additional criteria stipulated in the sub-protocols that are specific to the target candidate being tested (eg, criteria related to prohibited medications). In order to enrol, a patient or legally authorised representative must sign an informed consent form (ICF) and meet all entry criteria for both the Master Protocol and at least 1 respective sub-protocol.

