### **6.3 Measures to Minimise Bias: Randomisation and Blinding**

No blinding will be used in this study.

The study will randomise participants on an ongoing basis to receive either one of the active candidate treatment arms as an add-on to SoC or to receive SoC alone. Randomisation will be stratified by study centre and baseline severity grade.

If additional arms (candidate treatments) are added to or dropped from the study, randomisation will proceed with an equal probability of assignment to each of the remaining arms, except for situations where a patient does not meet the inclusion/criteria for, and hence would be excluded from, one or more of the sub-protocols.

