**Table 3 Analysis Sets**

| Analysis Set                       | Description                                                                                                                                                                                                                                                                                                            |
|------------------------------------|------------------------------------------------------------------------------------------------------------------------------------------------------------------------------------------------------------------------------------------------------------------------------------------------------------------------|
| Intention to Treat (ITT)           | All patients who are randomised and match the inclusion/exclusion criteria of the Master Protocol and relevant sub protocol.                                                                                                                                                                                           |
| Safety Set                         | All patients who are randomised and take at least 1 dose of study medication.                                                                                                                                                                                                                                          |
| Pharmacokinetic Analysis Set (PKS) | All patients who are randomised and take at least 1 dose of the candidate agent and have quantifiable candidate agent concentrations postdose without protocol deviations or events affecting the pharmacokinetic results.                                                                                             |
| Pharmacodynamic Analysis Set (PDS) | All patients who are randomised and take at least 1 dose of study medication (candidate agent or standard of care) and have evaluable results for at least 1 pharmacodynamic endpoint postdose. All analyses of the PDS will be based on each patient's randomised assigned treatment (not actual treatment received). |

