| Primary     | 
Stage 1:
 
Time to 2-point improvement on the 9-point ordinal scale, live discharge, or fit for discharge (as analysed at Day 29), whichever comes first, will be compared with each treatment arm with standard of care (SoC) using log-rank test at the one-sided 0.1 alpha level. Patients in the Stage 1 Intention to Treat (ITT) set will be used.
 
Stage 2:
 
The time to 2-point improvement on the 9-point ordinal scale, live discharge, or fit for discharge (as analysed at Day 29), whichever comes first, analyses will be conducted between the selected treatments plus SoC and SoC alone. The primary endpoint could be re-determined based on Stage 1 results. Patients in the Stage 2 ITT set will be used for the following analyses:
 
The time to 2-point improvement on 9-point ordinal scale, live discharge, or fit for discharge at Day 29 will be conducted between each selected treatment group and control using the log-rank statistic, stratifying for study centre and baseline severity grade, and the p-value associated with the log-rank statistic will be compared at the 2-sided 0.05 alpha level. The hazard ratio between treatment arm and SoC will be estimated using Cox regression, including treatment, age category (age <70 years vs ≥70 years), baseline severity, age category and treatment interaction, baseline severity and treatment interaction as fixed effect, and study centre as random effect.
 |

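### The stated control-group rule restricts an agent's controls by calendar period but not by eligibility for that agent, and the ITT wording does not clearly close the gap

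*Protocol*

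**What the plan says.** The only sentence that describes an agent's control group is in the synopsis and Section 4.1. It limits that group to the agent's randomisation period: "with the control group for a candidate agent including only patients randomised during the period in which the candidate agent group was randomised". The same sentence makes allocation depend on eligibility: "with patients being randomised equally (ie, 1:1:1...) to the sub protocols with inclusion/exclusion criteria that they meet".

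Three other places bear on the point.

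- **Section 5.0** asks a patient only to "meet all entry criteria for both the Master Protocol and at least 1 respective sub-protocol". The example it gives of added sub-protocol criteria is prohibited medication.
- **Section 6.3** gives equal probability to each open arm, "except for situations where a patient does not meet the inclusion/criteria for, and hence would be excluded from, one or more of the sub-protocols".
- **Table 3** defines ITT as "All patients who are randomised and match the inclusion/exclusion criteria of the Master Protocol and relevant sub protocol". The Safety Set in the same table requires randomisation and at least one dose of study medication, with no sub-protocol condition.

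In Table 4 the Stage 1 primary analysis is an unstratified log-rank test at one-sided 0.1: "Patients in the Stage 1 Intention to Treat (ITT) set will be used". Stage 2 uses the Stage 2 ITT set and a log-rank test stratified by centre and baseline severity.

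**The concern.** Take a patient who fails agent A's criteria but meets agent B's. That patient can be randomised to SoC while A is recruiting, and the period rule as written does not keep the patient out of A's controls. The patient had no chance of receiving A. Such patients are also over-represented in SoC, because an equal split over fewer open arms sends a larger fraction of them there.

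If what makes a patient ineligible for A also affects recovery, A's arm and its controls are different populations. A prognostic difference would then appear as a drug effect, or would hide one. The Stage 1 result that feeds progression, the Stage 2 confirmatory test and the safety comparison could all be affected.

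**Working it through.** **The plan's own figures.** Inputs from Section 9.3: Day 29 response 70% on SoC and 85.5% on the agent; one-sided 0.10 with 80% power (Stage 1); one-sided 0.025 with 90% power (Stage 2).

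- Implied HR = ln(1 − 0.855)/ln(1 − 0.70) = 1.604.
- Events (Schoenfeld, 1:1) = 4(z_α + z_β)²/(ln HR)² = 80.8 for Stage 1 and 188.3 for Stage 2. The plan has 81 and 188.
- Patients per arm = Freedman events/(0.70 + 0.855): 83.8/1.555 = 53.9 and 195.4/1.555 = 125.6. The plan has 54 and 126.

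The sample sizes reproduce and are not in question.

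**Share of controls who could not have received A.** Assumptions not in the documents: K = 3 agents open; a fraction q of patients is ineligible for A but eligible for the other two. SoC then receives 1/(K+1) = 1/4 of eligible patients and 1/K = 1/3 of ineligible ones.

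- Share f = (q/K)/[q/K + (1 − q)/(K+1)].
- q = 0.25: 0.0833/(0.0833 + 0.1875) = 0.308.
- q = 0.10: 0.0333/(0.0333 + 0.2250) = 0.129.

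**Apparent HR with no drug effect.** Further assumption: 70% response in eligible patients and 50% or 60% in ineligible ones.

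- Pooled SoC response at q = 0.25: 0.692 × 0.70 + 0.308 × 0.50 = 0.638; with 0.60 it is 0.669.
- HR = ln(0.30)/ln(1 − pooled response) = 1.183 and 1.088.

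**One-sided error, unstratified.** Agent fraction r = 0.1875/(0.1875 + 0.2708) = 0.409. Shift in Z = ln(HR) × √[d·r(1 − r)], with d = 81 or 188.

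| q | Ineligible response | Null HR | Stage 1 shift, error (nominal 10%) | Stage 2 shift, error (nominal 2.5%) |
|---|---|---|---|---|
| 0.25 | 60% | 1.088 | 0.37, 18% | 0.57, 8% |
| 0.25 | 50% | 1.183 | 0.75, 30% | 1.14, 20% |
| 0.10 | 60% | 1.036 | 0.16, 13% | 0.24, 4% |
| 0.10 | 50% | 1.074 | 0.32, 17% | 0.49, 7% |

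The 10% rows use r = 0.225/(0.225 + 0.2583) = 0.466. With equal numbers per arm (r = 0.5), the 20% becomes 21%.

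**Opposite direction.** If the ineligible respond at 85% and q = 0.25, pooled SoC response is 0.746 and the null HR is 0.878. A true HR of 1.6 then appears as 1.6 × 0.878 = 1.405, and Stage 2 power is about 63% against the planned 90%.

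**Simulation check.** Unstratified log-rank, exponential times, censoring at 28 days, 54 or 126 per arm, 8,000 null and 4,000 power replicates. Here f is the ineligible share of the SoC arm, and the hazard column is their response hazard relative to eligible SoC patients.

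| f | Relative hazard | Null rejection, Stage 1 | Null rejection, Stage 2 |
|---|---|---|---|
| 0 | – | 0.100 | 0.028 |
| 0.25 | 1.00 | 0.100 | 0.026 |
| 0.10 | 0.75 | 0.120 | 0.039 |
| 0.25 | 0.75 | 0.163 | 0.071 |
| 0.25 | 0.50 | 0.274 | 0.179 |
| 0.25 | 1.33 | 0.053 | 0.007 |

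Power is 0.80 and 0.91 at f = 0. In the last row it is 0.71 and 0.80.

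**The case against.** The strongest reply is that the period rule is not the only filter. Both primary analyses use ITT, and ITT requires a match to the relevant sub-protocol. In a comparison of A with SoC, the natural reading of that singular phrase is A's sub-protocol, which would remove the ineligible controls at both stages. The control-group sentence excludes non-concurrent controls; it does not say that every concurrent SoC patient is included. Section 9.5 also leaves the description of analysis sets to the SAP, with an addendum per sub-protocol.

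Much of this stands. A reader might infer that controls are matched on calendar period alone and that both stages are therefore biased. The documents do not support that, because the ITT wording can be read as a cure. It is not a secure one: an SoC patient belongs to no sub-protocol by allocation, and Section 5.0 lets *relevant* mean any sub-protocol the patient qualified for. Table 4 refers to one ITT set per stage, not one per comparison, and the Safety Set carries no such filter. The control-group rule itself is fixed in this document, so clarifying it is not merely SAP detail.

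A reader might also object that filtering on eligibility would be a post-randomisation selection. That need not follow. Section 8.0 requires screening to be completed to confirm eligibility, and Section 6.3 cannot operate unless eligibility for each open agent is known at allocation. Selecting on that status is valid. What is missing is a requirement to record it then, which matters in an unblinded trial.

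Four further limits stand.

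- Section 4.2 says only that "this study design enables continuation of the study even if an agent becomes unavailable". Arms closing centre by centre for lack of supply is not in the text, and the eligibility route does not depend on it.
- Stage 2 stratification by centre and severity removes the part of any difference that those factors explain.
- Master Protocol exclusions on liver, renal and cardiac grounds already apply to every patient.
- Section 9.6 rests Stage 1 progression on the totality of data, so the log-rank error is not a go/no-go error rate.

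**Conclusion.** The point holds as a gap in the control-group definition. Read literally, the period rule admits SoC patients who could not have received the agent. The ITT wording may exclude them from the primary analyses but does not say so clearly, and nothing excludes them from the safety comparison.

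Bias requires that such patients are counted and that their prognosis differs. It can go either way, and it is zero if prognosis is equal or if all open agents share the same criteria. The one-sided errors of about 18-30% in Stage 1 and 8-21% in Stage 2 rest on three open agents, 25% ineligible, 50-60% against 70% response, and an unstratified test. At 10% ineligible, the Stage 2 error is 4-7%. The Stage 2 figures are therefore overstated to the extent that centre and severity explain the difference; this was not quantified. The correction deserves to be made because it costs little, touches every agent's comparison, and depends on information that may not be recoverable without bias if it is not stored at allocation.

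**What to change.** In the synopsis, Sections 4.1 and 6.3 and Table 3, define each agent's control group, for both efficacy and safety, as the SoC patients who

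- were randomised in the same period and stage, and
- at randomisation met that agent's sub-protocol criteria and had that arm open to them.

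State in Table 3 that the relevant sub-protocol for an SoC patient is that of the agent being compared, so that one SoC patient may serve as a control for several agents. Require the randomisation system to store the set of arms open to each patient before allocation.

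The cost is a few sentences and one stored field. Fewer SoC patients will count for an agent with narrow criteria. Within every eligibility pattern, however, agent and SoC are allocated equally (1/2 to 1/2, 1/3 to 1/3, and so on), so the comparison stays 1:1. The plan's 54 patients [81 events] and 126 [188] per arm are unchanged, counted among eligible concurrent controls.

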## **4.2 Scientific Rationale for Study Design**

There are currently no approved therapeutic agents available to treat coronaviruses such SARS-CoV-2, the causative agent of as COVID-19 disease, and there is an urgent public health need for rapid development of such interventions. This adaptive platform study is designed to rapidly assess multiple candidate agents as treatments for COVID-19. Candidate drugs that are initially assessed as being efficacious will be moved from an evaluation (pilot) stage to a confirmatory stage, with candidate agents being added to and removed from the study on an ongoing basis, depending on the results of their evaluation. Patients to be included in the study will be hospitalised and may require either supplemental oxygen, noninvasive ventilation or high-flow oxygen devices.

This study utilises an adaptive design that maximises efficiency in identifying a safe and efficacious therapeutic agent for COVID-19. Some candidate agents may be in limited supply and this study design enables continuation of the study even if an agent becomes unavailable. In addition, the adaptive design allows for the evaluation of new candidate agents as they are identified.

## **4.3 Justification for Dose**

Justification for the dose of each candidate agent will be included in the corresponding sub-protocol.

## **4.4 End of Study Definition**

For each sub-protocol, the end of the study for that candidate agent will be defined as the date on which the last patient completes the last visit for that sub-protocol.

For the overall study, the end of the study will be defined as the date on which the last patient completes the last visit for the final sub-protocol to be concluded.

Once a patient has completed this study, there are no restrictions on them entering another study, subject to the eligibility criteria of that subsequent study.

## 5.0 STUDY POPULATION

Prospective approval of protocol deviations to recruitment and enrolment criteria, also known as protocol waivers or exemptions, is not permitted.

The inclusion and exclusion criteria listed below may be supplemented by additional criteria stipulated in the sub-protocols that are specific to the target candidate being tested (eg, criteria related to prohibited medications). In order to enrol, a patient or legally authorised representative must sign an informed consent form (ICF) and meet all entry criteria for both the Master Protocol and at least 1 respective sub-protocol.

### 5.1 Inclusion Criteria

Patients are eligible to be included in the study only if all of the following criteria apply (as well as all criteria from the appropriate sub-protocol):

1. Adults ( $\geq 18$  years) with SARS-CoV-2 infection confirmed by laboratory tests and/or point of care tests.
2. A score of Grade 3 to 5 on the 9-point ordinal scale.
3. The patient, and their partner(s), agree to use medically-accepted double-barrier methods of contraception (eg, barrier methods, including male condom, female condom or diaphragm with spermicidal gel) during the study and for at least 6 weeks after termination of study therapy. A vasectomised partner would be considered an appropriate birth control method provided that the partner is the sole male sexual partner and the absence of sperm has been confirmed. If not, an additional method of contraception should be used.  
or  
The patient is a woman who is not of childbearing potential (as defined in Appendix 5)
4. Women who are lactating who agree not to breastfeed their child during the study and for at least 6 weeks after termination of study therapy (they may continue to express milk away from the child during this period, but this milk must be discarded).
5. Ability to provide informed consent signed by the study patient or legally authorised representative.

